## Abstract

**Background:**

Postoperative delirium (POD) is a common and severe complication in elderly patients following gastrointestinal oncologic surgery, associated with prolonged hospitalization, increased morbidity and mortality, and substantial healthcare costs. The stellate ganglion block (SGB), a sympathetic nerve block with anti-inflammatory and autonomic-modulating effects, has shown promise in improving perioperative outcomes. However, high-quality randomized controlled trials evaluating its efficacy in preventing POD in this older population are lacking.

**Methods:**

This is a single-center, prospective, randomized, double-blind (participants and outcome assessors), sham- controlled trial. A total of 174 elderly patients (≥60 years) scheduled for elective radical gastrointestinal cancer surgery will be randomized in a 1:1 ratio to receive either two ultrasound-guided SGBs (one on the afternoon before surgery and one 30 min before anesthesia induction) with 0.375% ropivacaine (3–5 mL each) or a sham block with normal saline (3–5 mL). All patients, surgeons, and outcome assessors will be blinded to group assignment. A standardized anesthesia protocol and a multicomponent delirium- prevention bundle will be applied to all participants. The primary outcome is the cumulative incidence of POD within postoperative days 1–3, assessed twice daily using the 3-Minute Diagnostic Interview for CAM-defined Delirium (3D-CAM). Secondary outcomes include delirium severity and duration, postoperative recovery (Quality of Recovery-15 score), inflammatory biomarkers (procalcitonin, C-reactive protein (CRP), interleukin-6 (IL-6), lymphocyte-to-monocyte ratio [LMR], neutrophil-to-lymphocyte ratio [NLR]), pain trajectories, opioid consumption, and length of hospital stay.

**Expected outcomes:**

We hypothesize that preoperative SGB will reduce the incidence and severity of POD compared to a sham block. This study will provide preliminary evidence on the feasibility and efficacy of SGB as a targeted intervention for high-risk older surgical oncology patients, while acknowledging that the assumed effect size may be optimistic.

**Clinical trial registration:**

https://www.chictr.org.cn/showproj.html?proj=302103, identifier: ChiCTR2600118223.

## Introduction

1

### Background and rationale

1.1

Postoperative delirium (POD) is an acute, fluctuating neuropsychiatric syndrome characterized by disturbances in attention, consciousness, and cognition (1). Among elderly patients (≥60 years) undergoing surgery for gastrointestinal malignancies, POD occurs in 35%~48% of cases and is consistently associated with poor outcomes, including increased risk of postoperative complications, prolonged hospitalization, institutionalization, long-term cognitive decline, and mortality (2–4). Despite these profound consequences, effective pharmacological prevention strategies remain limited, particularly in the geriatric surgical population (5).

Current clinical practice primarily relies on non-pharmacologic interventions such as multicomponent prevention bundles (e.g., the ABCDEF approach) (6), yet these strategies alone cannot fully mitigate POD risk in older adults. Given the multifactorial pathophysiology of POD, including neuro-inflammation (7), autonomic dysregulation (8), and impaired cerebral perfusion (9), novel strategies targeting neuro-inflammation and sympathetic over-activity are needed, especially for elderly patients at higher risk.

### Stellate ganglion block as a promising intervention

1.2

The stellate ganglion is a key sympathetic structure. Ultrasound-guided stellate ganglion block (SGB) is a minimally invasive procedure that transiently inhibits sympathetic outflow (10). Preclinical and emerging clinical evidence suggests that SGB may confer neuroprotective benefits by: (1) modulating systemic and neuro-inflammation through cytokine regulation (11); (2) improving cerebral blood flow via vasodilation (12); (3) attenuating perioperative stress and hyper-adrenergic states (13). These mechanisms align closely with proposed pathways of POD pathogenesis. Recent studies have reported that SGB may reduce postoperative pain, inflammatory markers, and incidence of postoperative cognitive dysfunction (POCD) in animal models (14, 15). Meanwhile, it is important to note that these studies focused on POCD and other perioperative outcomes, not directly on POD. Direct evidence for SGB preventing POD in humans remains limited, and the available studies are small in sample size or still at the protocol stage. However, there is a paucity of rigorous, blinded, randomized controlled trials specifically designed to evaluate the efficacy of SGB for preventing POD in elderly patients undergoing major gastrointestinal oncologic surgery (16, 17). This study aims to address this evidence gap.

## Study objectives

2

### Primary objective

2.1

To compare the effect of preoperative ultrasound-guided SGB versus sham block on the 3-day cumulative incidence of POD, following a protocol of two blocks: the first administered on the afternoon before surgery, and the second administered 30 min before anesthesia induction.

### Secondary objectives

2.2

To evaluate the effects of SGB on delirium severity and duration, postoperative recovery (Quality of Recovery-15 score), inflammatory biomarkers (procalcitonin, C-reactive protein (CRP), interleukin-6 (IL-6), lymphocyte-to-monocyte ratio [LMR], neutrophil-to-lymphocyte ratio [NLR]), pain trajectories, opioid consumption, and length of hospital stay.

### Hypothesis

2.3

We hypothesize that patients receiving preoperative SGB will exhibit a significantly lower incidence and severity of POD, attributable to its anti-inflammatory and autonomic-modulating properties.

## Methods

3

### Study design and setting

3.1

This is a prospective, randomized, double-blind, sham-controlled, single-center trial conducted at t the Second Hospital & Clinical Medical School, Lanzhou University. The protocol adheres to the SPIRIT 2025 and CONSORT 2025 guidelines.

#### Trial registration and recruitment status

3.1.1

This study was registered with the Chinese Clinical Trial Registry (ChiCTR) before the enrollment of the first participant (Registration No. ChiCTR2600118223). As of the time of manuscript submission, no participants have been enrolled or randomized. Recruitment is planned to take place from February 5, 2026, to March 1, 2027.

### Participants

3.2

The participant enrollment and study workflow are detailed in Figure 1.

**Figure 1 fig1:**
[figure not shown]
CONSORT 2025 flow diagram (22).

#### Inclusion criteria

3.2.1

(1) Age ≥ 60 years.(2) Scheduled for elective open or laparoscopic radical resection of gastric or colorectal cancer.(3) American Society of Anesthesiologists (ASA) physical status I-III.(4) Ability to provide written informed consent (or through a legal representative).

#### Exclusion criteria

3.2.2

(1) Preexisting cognitive impairment (Montreal Cognitive Assessment score below education-adjusted cutoff) or diagnosed dementia.(2) Severe visual/hearing impairment or language barrier precluding reliable delirium assessment.(3) Major psychiatric disorders (e.g., schizophrenia, bipolar disorder).(4) Contraindications to SGB: local infection at the puncture site, known allergy to local anesthetics, severe coagulopathy, or therapeutic anticoagulation that cannot be safely paused.(5) Severe systemic disease: Child-Pugh C liver cirrhosis, end-stage renal disease (eGFR <30 mL/min/1.73 m^2^ or on dialysis), NYHA class III-IV heart failure.(6) Emergency surgery, anticipated surgery duration <2 h or >6 h.(7) History of substance abuse.

### Randomization and blinding

3.3

Participants will be randomized in a 1:1 ratio to the SGB or sham group using computer- generated, permuted block randomization (block sizes of 4 and 6). Allocation will be concealed using sequentially numbered, opaque, sealed envelopes (SNOSE) prepared by an independent statistician. The envelope will be opened only by the research nurse preparing the study syringe.

This study is double-blind with respect to participants and outcome assessors. Participants, surgeons, postoperative care teams, and outcome assessors will be unaware of group allocation. The anesthesiologist performing the block will not be blinded due to the potential physical signs of a successful block (e.g., Horner’s syndrome) but will have no role in postoperative assessments or data collection.

Although successful SGB may produce visible signs such as Horner’s syndrome (ptosis, miosis, anhidrosis), these signs are typically ipsilateral and may be noticeable to the participant and potentially to the assessor. To evaluate the success of blinding, the following measures will be implemented:

(1) Participant blinding assessment: Within 24 h after the final postoperative delirium assessment, participants will be asked to guess their group assignment (SGB/sham/uncertain). The proportion of correct guesses will be compared between groups using a chi-square test to assess whether blinding was maintained.(2) Assessor blinding assessment: Outcome assessors will be asked to document any suspicion of group allocation (and the reason, e.g., observed Horner’s syndrome) after completing each participant’s delirium assessments. The frequency of suspected unblinding will be reported.(3) Mitigation strategies: To minimize unblinding, assessors will be instructed to avoid direct eye contact focused on the participant’s pupillary status and to focus on standardized assessment procedures. Participants will be instructed not to discuss any periprocedural sensations (e.g., facial warmth, ptosis) with assessors.

Results of the blinding effectiveness assessment will be reported alongside the primary outcome as a secondary analysis.

Unblinding will be permissible only in the event of a serious adverse event where knowledge of the intervention is crucial for clinical management. The unblinding procedure will be overseen by the principal investigator.

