##### Absence of specific sympathetic blockade effect

3.4.3.2

Normal saline lacks the nerve conduction blocking effect of local anesthetics and therefore does not produce the specific sympathetic inhibitory effects of SGB (e.g., ipsilateral skin temperature increase, Horner’s syndrome). It has no specific therapeutic effect, consistent with the basic definition of a sham control.

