#### Systematic adverse event reporting

3.5.6

Mild adverse events (e.g., transient hoarseness, mild dysphagia, local pain) will be recorded by the operating physician within 24 h using an adverse event reporting form and reported to the study coordinator.

Serious adverse events (e.g., LAST, severe hematoma, pneumothorax, nerve injury, death) will be reported to the ethics committee, DSMB, and institutional adverse event management department within 24 h of discovery.

All adverse events will be documented with details on time of occurrence, severity, management measures, and outcomes. Regular summary reports will be submitted to the DSMB for review.

Stopping rule: If two or more serious adverse events directly related to SGB occur, the DSMB may recommend early termination of the study.

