##### Stopping rules for SGB-related adverse events

3.10.2.6

The study may be terminated if any of the following criteria are met:

Two or more SGB-related serious adverse events occur, including LAST, severe cervical hematoma, pneumothorax, persistent recurrent laryngeal nerve palsy, or intrathecal drug spread. The incidence of serious adverse events in the SGB group exceeds the pre-specified safety threshold of 5%, and the DSMB determines that this risk cannot be mitigated by modifying procedures or enhancing monitoring. The interim analysis shows a significantly higher total adverse event rate in the SGB group compared to the sham group (*p* < 0.05), and the difference is clinically meaningful, indicating unacceptable safety risks. A major safety hazard is identified in the SGB procedure that cannot be corrected through protocol amendments. Data fabrication or serious protocol violations occur that compromise data integrity and cannot be rectified.

If any of the above criteria are met, the DSMB will issue a written recommendation to suspend enrollment, modify the protocol, or terminate the trial. After the DSMB recommends termination, a written report will be submitted to the ethics committee and the Chinese Clinical Trial Registry. The study team will immediately stop participant recruitment and intervention, complete follow-up of enrolled participants to ensure their safety, and report to relevant authorities as required.

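### The participant blinding check tests whether the two arms have the same percentage of correct guesses, which is not the hypothesis that blinding held

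*Protocol article*

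**What the plan says.** Section 3.3 (Randomization and blinding) sets out one participant question and one test. On the question: "Within 24 h after the final postoperative delirium assessment, participants will be asked to guess their group assignment (SGB/sham/uncertain"). On the test: "The proportion of correct guesses will be compared between groups using a chi-square test to assess whether blinding was maintained". The results are to be reported beside the primary outcome as a secondary analysis. Outcome assessors separately note any suspicion of allocation and the reason for it, and the frequency is reported without a test.

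The same section says of Horner's signs that "these signs are typically ipsilateral and may be noticeable to the participant and potentially to the assessor". Section 3.4.1 confirms a successful block by Horner's syndrome and/or ipsilateral warming of at least 1.5 °C within 15 minutes. Section 3.4.3.2 says saline "does not produce the specific sympathetic inhibitory effects of SGB (e.g., ipsilateral skin temperature increase, Horner’s syndrome").

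On roles, section 3.3 says that the unblinded anesthesiologist who performs the block "will have no role in postoperative assessments or data collection". Section 3.5.6 says that mild adverse events "will be recorded by the operating physician within 24 h using an adverse event reporting form". Section 3.10.2.6 lists among its stopping criteria: "The interim analysis shows a significantly higher total adverse event rate in the SGB group compared to the sham group", at p < 0.05 and if clinically meaningful.

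**The concern.** Blinding has held, as far as a guess can show it, when the guess is unrelated to the arm. The planned test asks instead whether the two arms are equally often right. The two questions can have opposite answers.

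- **Both arms guess well.** Warmth or ptosis points to SGB and its absence points to sham, so both arms can be right at a similar high rate. The planned comparison then shows no difference.
- **Both arms lean the same way without information.** If most participants in either arm say SGB, most of the SGB arm is right and most of the sham arm is wrong. The planned comparison then shows a large difference although nobody was unblinded.

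At stake is how far readers can trust an interview-based delirium outcome. The Discussion relies on this check so that readers can judge blinding success.

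The second, smaller matter is who records mild adverse events. The term in section 3.5.6 is not defined. If it means the block operator, a person who knows the allocation supplies part of the total adverse event comparison.

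**Working it through.** **Inputs.** Arm size is from section 3.8: 78 / 0.90 = 86.7, so 87 per group. (The 78 correct guesses used below are 90% of 87 and have nothing to do with the 78 of the sample size.) The document gives no figure for the blinding check to reproduce and no guess distribution, so every distribution here is an assumption.

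**The two null hypotheses.** Let a be the probability of guessing SGB in the SGB arm and b the same probability in the sham arm, with no uncertain answers.

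- Intact blinding: a = b.
- Planned test: a = 1 − b, because a correct sham guess has probability 1 − b.

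Both hold together only at a = b = 0.5. Anywhere else, the truth of one means the falsity of the other.

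**Formulas.** Pearson chi-square without continuity correction. For a table with rows (x, y) and (y, x), n = 87 per row and 174 in total, it reduces to 174 × ((x − y)/87)². Bang's index per arm is (correct − incorrect)/n.

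**Both arms 90% correct.** 0.90 × 87 = 78.3, so 78.
- Planned test, 78/87 v 78/87: difference 0, p = 1.00.
- Guess by arm, rows (78, 9) and (9, 78): 174 × (69/87)² = 109.4, p about 1e-25.

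**80% of both arms say SGB, unrelated to arm.** 0.80 × 87 = 69.6, so 70.
- Planned test, 70/87 v 17/87 correct: 174 × (53/87)² = 64.6, p about 9e-16.
- Guess by arm, both rows (70, 17): p = 1.00.

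**70% of both arms say SGB.** 0.70 × 87 = 60.9, so 61.
- Planned test, 61/87 v 26/87 correct: 174 × (35/87)² = 28.2, p about 1e-7.
- Guess by arm: p = 1.00.

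**Range of assumptions:**

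| Assumed guesses | Correct, SGB v sham | Planned test p | Guess-by-arm p | Bang's index, SGB / sham |
|---|---|---|---|---|
| About 99% right in both arms | 86 v 86 | 1.00 | 5e-38 | 0.98 / 0.98 |
| 90% right in both | 78 v 78 | 1.00 | 1e-25 | 0.79 / 0.79 |
| 80% right in both | 70 v 70 | 1.00 | 9e-16 | 0.61 / 0.61 |
| 70% say SGB in both | 61 v 26 | 1e-7 | 1.00 | 0.40 / −0.40 |
| 60% SGB, 30% sham, 10% uncertain in both | 52 v 26 | 7e-5 | 1.00 | 0.30 / −0.30 |
| 90% right in SGB arm, 50% in sham arm | 78 v 44 | 2e-8 | 8e-9 | 0.79 / 0.01 |

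In repeated simulated trials the planned test rejects about 5% of the time at a true 90% correct in both arms and about 1% at 99%. It rejects in about 100% when 70% of both arms say SGB, and in about 98% under the 60/30/10 split. At exactly 87/87 correct in both arms the statistic is undefined, because no one is incorrect.

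**Adverse events, passages side by side.** Section 3.5.6 sits in the block-safety section, its examples (hoarseness, dysphagia, local pain) fit a neck block, and section 3.5.1 calls the person doing the block the operator. Section 3.10.2.5 confirms that SGB operators are not blinded. Read that way, 3.5.6 contradicts 3.3. But the term can equally mean the surgeon, whom 3.3 keeps blinded, and then there is no contradiction.

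**The case against.** A reader might infer that the plan would declare complete unblinding to be maintained blinding. The document does not say so. It states no rule that a non-significant result means success, the statistic is undefined when everyone is right, and a careful reader who saw 90% correct in both arms would not be reassured.

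A reader might also infer that symmetric unblinding is the expected case. Nothing in the document supports that. SGB participants may notice signs while sham participants answer uncertain or guess at random, and the planned test does pick up unblinding of that asymmetric kind (78/87 v 44/87, p about 2e-8).

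The assessor check, arguably the more relevant one for an assessor-rated outcome, is descriptive and free of this flaw. Blinding is the sixth of six limitations in the Discussion, not the leading one. Asking for the guess earlier as well is a preference: a question after the last assessment covers the whole period at risk, and an early one could draw attention to allocation.

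On adverse events, a reader might infer that unblinded recording biases a rule that can stop the trial. That depends on an undefined term. Ward nurses also monitor for up to 24 hours, and the criterion requires clinical relevance and leads to a DSMB recommendation, not to an automatic stop.

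All of this stands and limits the point. None of it makes equal percent-correct the right hypothesis for the stated purpose.

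**Conclusion.** The test is wrong as written for the purpose given to it. It returns p = 1.00 at any equal percent-correct below 100%, however high. It returns p between about 9e-16 and 7e-5 under uninformative guessing with a shared lean of 60% to 80% towards SGB. The sizes rest on 87 per arm and on assumed guess distributions, only one of which includes uncertain answers, so they illustrate the failure and do not predict the trial's result. Whether the arms would guess symmetrically is unknown.

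The consequence is confined to a secondary analysis. The primary estimate, its p-value and the sample size are untouched.

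The adverse event point is conditional. Sections 3.3 and 3.5.6 contradict each other only if the operating physician is the block operator, and the document does not settle that.

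**What to change.** In section 3.3, replace the between-arm test of percent-correct with the full table of guess (SGB, sham, uncertain) by allocated arm, and Bang's blinding index for each arm with its 95% CI. Two clearly positive indices indicate unblinding in both arms, one positive and one near zero indicates unblinding in one arm, and values of opposite sign and similar size indicate a shared lean. The data are those already planned, so the cost is a change of wording.

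In section 3.5.6, state who the operating physician is and reconcile the sentence with section 3.3 by naming a blinded recorder from existing staff. Ward staff who already monitor after the block are one possibility, since section 3.3 keeps the postoperative care teams blinded. The delirium assessors are less suitable, because block complications could hint at allocation. The cost is one sentence and, if the block operator was meant, a reassigned task. No participant had been enrolled at submission, so both changes can be made before data exist.

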### Interventions

3.4

#### Active intervention (SGB group)

3.4.1

Patients in this group will receive two stellate ganglion blocks: The first block will be performed on the afternoon before surgery. The second will be performed 30 min before the induction of general anesthesia on the day of surgery.

Lateralization: All blocks will be performed on the right side at the C6 level. The right side is selected for the following reasons: (1) right-sided SGB is associated with a lower risk of esophageal injury and has a more predictable anatomical relationship between the stellate ganglion and adjacent structures; (2) right-sided sympathetic blockade may have a more favorable effect on cardiac autonomic balance (reducing sympathetic outflow to the heart) compared to left-sided block; (3) previous pilot studies on SGB for perioperative neurocognitive outcomes predominantly used right-sided approach, facilitating comparison with existing literature.

Under sterile conditions and real-time ultrasound guidance (C6 level), a 22-gage needle will be advanced to the prevertebral fascia. After negative aspiration, 3–5 mL of 0.375% ropivacaine will be injected (Figure 2). Successful blockade will be confirmed by the development of Horner’s syndrome (ptosis, miosis, anhidrosis) and/or ipsilateral skin temperature increase ≥1.5 °C within 15 min.

**Figure 2 fig2:**
[figure not shown]
Ultrasound-guided stellate ganglion block. SCM, sternocleidomastoid muscle; IJV, internal jugular vein; CA, carotid artery; AS, anterior scalene; VV, vertebral vein; VA, vertebral artery; SG, stellate ganglion; LCM, longus colli muscle.

#### Sham intervention (control group)

3.4.2

An identical procedure will be performed at the corresponding time points (on the afternoon before surgery and 30 min before anesthesia induction on the surgery day), including skin disinfection, ultrasound imaging, and needle placement. The syringe will contain 3–5 mL of normal saline (0.9% NaCl). No local anesthetic will be administered. The rationale for using normal saline as the sham control is provided in section 3.4.3.

